#### Follow-up

All participants are followed up 3 months after the Health Check. Participants are asked to wear an accelerometer (Actigraph GT3X+ or Actigraph w-GT3X-BT) 1 around their waist for a period of 7 consecutive days, putting it on in the morning and taking it off before going to bed. Participants are encouraged to go about their activities as normal during this time but are asked to log the times of wear during the day (i.e. the time the monitor was put on and taken off) on the log sheet provided. At the end of the 7 days, participants return the accelerometer in the reply-paid envelope provided along with the log sheet and a completed questionnaire. Based on daily variability findings from the previous trial (Pears S, Bijker M, Morton K, Vasconcelos J, Parker RA, Westgate K, et al.: A randomised controlled trial of three very brief interventions for physical activity in primary care, submitted), a minimum of 3 days of activity data each with a minimum of 10 hours of wear-time data are required to count as a valid recording regardless of how many of the provided days are weekend days or weekdays. Participants are asked to re-wear the accelerometer if the returned data fail to reach this minimum. Non-wear time is determined by 90 minutes or more of zero counts.

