#### Primary outcome

The primary outcome is PA (total body movement) measured by tri-axial accelerometry (Actigraph GT3X+ or Actigraph w-GT3X-BT, ActiGraph, Pensacola, Florida, USA) expressed as average vector magnitude acceleration (counts per minute). Data collected at 60Hz will be integrated into 10-second epochs. Non-wear time, defined as strings of 90 minutes of consecutive zeros (on the vertical axis), will be excluded, and the remaining vector magnitude data will be summarised into average acceleration (counts per minute (cpm)).

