### Sample size

A trial of 394 participants per arm followed up is sufficient to detect a 0.2 sd (‘small’) difference in mean activity between arms (40 accelerometer cpm) based on the standard deviation of 200 cpm estimated in the previous trial) with 80 % power. However, allowing for attrition of 30 % at follow-up (i.e. 30 % of participants not providing sufficient accelerometer data), an initial sample size of 570 per arm would give 80 % power to detect an effect of this size between the two conditions (alpha = 0.05, two-sided test).

Recruitment and attrition will be monitored. If attrition is lower than 30 % and we anticipate achieving follow-up of 394 participants per arm with sufficient accelerometer data from randomising fewer than 570 per arm, participant recruitment will be closed.

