### Statistical analyses

Full details of the statistical methods are provided in the statistical analysis plan. The following is a summary of the main analyses proposed.

We will use analysis of covariance to test for intervention effects on continuous outcomes and quantify these with differences in means and 95 % confidence intervals, adjusting for primary care practice, gender and age. Logistic regression will be used for binary outcomes. An intention-to-treat approach will be used, supported by a per protocol analysis for the primary outcome analysis. All significance tests will be two-sided and assessed at the 5 % level of significance.

Missing data in the primary outcome will be handled within a sensitivity analysis considering optimistic and pessimistic scenarios for the intervention effect size in those with missing data and incorporating baseline predictors of primary outcome missing status that are differential by group. This analysis will be undertaken to examine the robustness of the main analysis result to the ‘missing at random’ (MAR) assumption. The aim is to adequately explore the impact of departures from the MAR assumption on the primary outcome results [27].

Pre-specified subgroup variables will be examined in relation to the primary outcome and will involve an initial test of differential intervention effect across the subgroup variable before summarising the intervention effect within the subgroup categories. These subgroup variables will include baseline cardiovascular risk, gender, age (40–59; 60–74 years), ethnic group, educational qualifications, employment status, household income, marital status, home ownership, vehicle ownership, and deprivation score (Index of Multiple Deprivation (IMD) 2007, derived from the participant’s home postcode [28]). For a continuous moderator such as CVD risk, the intervention effect observed in the highest tertile of the moderator will be estimated with a 95 % confidence interval having an informative width of +/- 25 thousand activity counts per day.

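### The precision promised for the top-tertile effect (±25 thousand counts per day) is not in the primary outcome's unit and does not follow from the plan's own SD and sample size, which give about ±48 cpm

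*Protocol article*

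**What the plan says.** The Primary outcome section defines the endpoint as average vector magnitude acceleration in counts per minute over wear time. The Sample size section uses the same unit: "394 participants per arm followed up is sufficient to detect a 0.2 sd" difference, given as "40 accelerometer cpm" and resting on a "standard deviation of 200 cpm estimated in the previous trial", with 80% power and "alpha = 0.05, two-sided test". It then allows for 30% attrition and arrives at 570 randomised per arm. Recruitment may close earlier if 394 per arm with sufficient data are anticipated.

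The Statistical analyses section examines the subgroup variables in relation to this primary outcome. A test of differential effect comes first and within-category summaries follow. For a continuous moderator it adds that the interval for the top-tertile effect is expected to be one "having an informative width of +/- 25 thousand activity counts per day".

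Counts per day is not among the accelerometer measures in Table 2. The article gives no SD in that unit and no mean wear time. The only wear-time figure is in the Follow-up section: at least 3 days, each with "a minimum of 10 hours of wear-time data are required to count as a valid recording". Participants are told to wear the monitor from morning until bedtime.

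**The concern.** The promise is a specific number about the primary outcome in a unit that the plan uses nowhere else, so a reader cannot set it beside the 40 cpm target. When it is converted over plausible wear times, the plan's SD and follow-up number give a wider interval than the one promised.

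The practical risk is one of interpretation. The plan calls this interval informative. If its half-width is larger than the effect the trial was designed to detect, a true effect of target size in the highest-risk third would usually give an interval that includes zero. A reader relying on the stated precision could take that as evidence of no benefit in this group.

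**Working it through.** **Inputs.** From Sample size: 394 followed up per arm, SD 200 cpm, target 40 cpm, 80% power, two-sided 5%, 30% attrition, 570 randomised per arm. From Statistical analyses: highest tertile, half-width 25,000 counts per day. Assumed, because the article does not state them: mean wear of 10 to 16 hours a day, and a tertile SD equal to the overall 200 cpm.

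**The plan's own sample size.** A two-sample t-test for 0.2 SD at 80% power needs 393.4 per arm, rounded up to 394; power at 394 is 0.80. Attrition: 394 / 0.7 = 563, against 570 stated (570 × 0.7 = 399). The primary calculation reproduces, so 200 cpm and 394 are the right inputs for the check.

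**Tertile half-width.**
- Tertile size per arm: 394 / 3 = 131.3.
- Standard error: 200 × √(2 / 131.3) = 24.7 cpm.
- Half-width: 1.96 × 24.7 = 48.4 cpm, which is 48.4 / 40 = 1.21 times the target difference.
- With 399 per arm followed up it is 48.1 cpm.
- Chance that the interval excludes zero on the side of benefit if the true tertile effect is 40 cpm: Φ(40 / 24.7 − 1.96) ≈ 0.37.

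**Conversion to counts per day** (cpm × minutes worn). The R² column is the share of variance that covariates would have to explain to reach ±25 thousand, that is 1 − (promised cpm / 48.4)².

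| Mean wear | ±25,000 per day in cpm | ±48.4 cpm in counts per day | Ratio to promise | R² needed | Followed up per arm needed |
|---|---|---|---|---|---|
| 10 h | 41.7 | 29.0 thousand | 1.16 | 26% | 532 |
| 12 h | 34.7 | 34.8 thousand | 1.39 | 48% | 765 |
| 14 h | 29.8 | 40.6 thousand | 1.63 | 62% | 1,041 |
| 16 h | 26.0 | 46.4 thousand | 1.86 | 71% | 1,360 |

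The last column is 6 × (1.96 × 200 / promised cpm)², rounded up. The two figures agree when wear is 25,000 / 48.4 = 517 minutes, or 8.6 hours.

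**More favourable readings.**
- All 570 per arm retained (190 per arm in the tertile): 1.96 × 200 × √(2 / 190) = 40.2 cpm. That is ±24.1 thousand at 10 h, ±29.0 thousand at 12 h and ±33.8 thousand at 14 h.
- A linear treatment-by-moderator model evaluated at the top-tertile mean, assuming a normal moderator (mean 1.09 SD above centre): 48.4 × √((1 + 1.09²) / 3) = 41.3 cpm. The ratio to the promise is 0.99 at 10 h, 1.19 at 12 h, 1.39 at 14 h and 1.59 at 16 h.

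**The case against.** Four points deserve weight.

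First, the sentence sizes nothing. The primary test, estimate and recruitment target do not depend on it. This stands, and it limits the severity.

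Second, the plan already puts a test of differential effect before any within-subgroup summary, and no rule draws a conclusion from the tertile interval alone. This also stands. The misreading is a risk created by the stated precision and is not something the plan prescribes.

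Third, the conversion is approximate. Mean wear is not given, and the 10-hour rule says what makes a recording valid; the article does not say that shorter days within a valid recording are dropped, so 10 hours is not a documented floor on the mean. Multiplying a cpm SD by one fixed wear time also ignores variation in wear between people. The article refers to a separate analysis plan that may hold a basis for the figure. These points make the ratio uncertain, but they leave the ±48 cpm untouched because it needs no conversion. A mean of 8.6 hours is also hard to square with morning-to-bedtime wear.

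Fourth, a reader might infer that ±25 thousand could not be met under any circumstances. The documents do not support that. At exactly 10 hours of wear it could just be met with covariates explaining about 26% of variance, with near-full retention of 570 per arm, or with a linear-interaction estimate. These routes are narrow. At 12 hours or more the last two miss, and covariates would have to explain about half the variance or more. The adjustment set is practice, gender and age, with no baseline accelerometry. Near-full retention would also run against the rule that lets recruitment close once 394 per arm are anticipated.

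**Conclusion.** The point holds as a unit inconsistency and an unsupported precision figure. On the plan's own SD and follow-up number, the top-tertile half-width is about ±48 cpm, larger than the 40 cpm target. This assumes a tertile SD of 200 cpm, about 131 per arm in the tertile and no gain from covariates. The statement that this is 1.2 to 1.9 times the promised width is conditional on a mean wear of 10 to 16 hours a day, which is an assumption.

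Two further inferences should not be drawn. The article shows no derivation of the ±25 thousand, so nothing in it supports an account of how the figure arose, such as a calculation that left out the division into tertiles. Nor does the error reach the main design: the 394 per arm reproduces and is unaffected. Severity is minor to moderate.

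**What to change.** - Restate the subgroup precision in the primary outcome's unit: about ±48 cpm for 131 per arm at SD 200 cpm, before covariate adjustment. Alternatively, keep counts per day but correct the figure from a stated SD in that unit and a stated mean wear time.
- Remove the description of the interval as informative, or say alongside it that the half-width exceeds the 40 cpm target difference.
- Present the tertile estimate as descriptive, and say that conclusions about moderators rest on the test of differential effect that is already planned.
- If the analysis plan carries the same sentence, change it there too.

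The cost is a few words and a less favourable figure. No data, participants or changes to the primary analysis are needed.

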## Discussion

The main aims of the VBI trial are to estimate the effectiveness and the cost-effectiveness of the Step It Up intervention delivered at the end of an NHS Health Check compared with the Health Check alone. The findings of this trial will extend the evidence base on very brief interventions for PA and will inform policy decisions about the introduction of very brief PA interventions into primary care consultations.

The trial has been designed to maximise both internal and external validity. The participant is randomised by a web-based program during the consultation. At point of entry into the trial (i.e. as informed consent is obtained), neither the participant nor the practitioner is aware of the group allocation. Once the participant is allocated, the practitioner tells them which group they are in. In a trial such as this, practitioners and participants cannot be blinded to the group allocation.

With individual randomisation of participants (as opposed to cluster randomisation of practitioners or practices), the risk that some of the content of the very brief intervention may be incorporated into the Health Check and that participants in the control arm may therefore receive some intervention content does exist. However, this did not occur in our trial of a practice nurse-delivered intervention for medication adherence [32]. The CRF and the written Step It Up intervention material have been designed to act as a prompt and guide to the consultation, thus minimising the risk of contamination. Audio-recording a sample of consultations will enable fidelity of delivery to be checked.

The primary outcome measure for this trial is PA objectively measured using an accelerometer at 3-month follow-up and expressed in activity counts per minute. Analysis of accelerometer data will be blinded. Secondary outcomes include self-report measures of PA, which provide information on the type and pattern of activity not otherwise obtainable from accelerometry.

After careful consideration, we decided not to measure the primary outcome at baseline. A baseline measure would have a number of advantages: sample size could be reduced, and an analysis of individual change scores would be possible. However, pilot work undertaken in preparation for this trial identified two potential problems arising from objective measurement of PA at baseline. First, baseline measurement is logistically difficult and may compromise uptake of the NHS Health Check and the flow of participants through the trial. Second, baseline accelerometry could act as an intervention; that is, some participants may increase their activity as a result of wearing the device, leaving less scope for our very brief intervention to have an effect [33].

The Step It Up intervention was chosen after a rigorous selection process [10] and evaluation in a previous trial (Pears S, Bijker M, Morton K, Vasconcelos J, Parker RA, Westgate K, et al.: A randomised controlled trial of three very brief interventions for physical activity in primary care, submitted) (ISRCTN02863077). The intervention is well characterised in terms of the component BCTs, is feasible to deliver in practice with limited training and is acceptable to both practitioners and participants. External validity is further increased by using nurses and healthcare assistants already trained to carry out NHS Health Checks.

The trial team brings together expertise in behavioural science, intervention development and evaluation, measurement of PA, medical statistics, health economics, and the design, conduct and analysis of primary care trials. In designing this trial, we have drawn on our previous work and on the guidelines and principles of trial reporting laid out in SPIRIT [34] and CONSORT [35]. See Additional file 1 for the SPIRIT Checklist.

## Trial status

Participant recruitment for this trial is underway.

## Abbreviations

BCT, behaviour change technique; CMO, chief medical officer; CRF, case report form; GP, general practice or general practitioner; GPPAQ, GP PA questionnaire; ICER, incremental cost-effectiveness ratio; IMD, Index of Multiple Deprivation; MAR, missing at random; MET, Metabolic Equivalent of Task; NHS, National Health Service; NICE, National Institute for Health and Care Excellence; PA, physical activity; PAEE, physical activity energy expenditure; PPI, patient and public involvement; RPAQ, Recent Physical Activity Questionnaire; VBI, very brief intervention; WPAI, Work Productivity and Activity Impairment
